### 10.8 Hospital discharge

Whether the patient was discharged home or not will be tabulated overall and by treatment group for the FAS population. Supportive listings will be provided.

### 10.9 Primary and Secondary Efficacy Analyses

#### 10.9.1 Primary analysis

The DFS will be summarized by treatment group. 95% confidence intervals will also be provided. The effect of ketorolac will be assessed by comparing the 2 treatment groups by a log rank test.

Potential need for adjustment regarding the inclusion criteria defining the ‘high risk’ profile of the patient, i.e high NLR AND/OR lymph nodes invasion AND/OR triple negative histopathology.

This summary will be reported using the FAS population and repeated for the PP population.

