### 4.5 Sample Size Determination

Sample size estimation is presented in the protocol. Patient numbers were based on the following assumptions:

Based on a reduction of recurrence of 33%, with a type I error of 5% and a power of 80%, the number of patients eligible is of 200 (Log Rank test), randomized in a 1:1 ratio between ketorolac and placebo.

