### 4.6 Randomization

This is a double blind study. Eligible patients will be randomized into the treatment arms with a ratio of 1:1 (ketorolac: placebo) as follows: Randomization will be performed 2 to 4h before surgery. A number will be assigned to each patient, as well as a treatment number, corresponding to ketorolac (30mg) or placebo (NaCl 0.9% 3 mL). Both are identical looking. In case of emergency, an unblinding envelope will be available. In both treatment groups, the randomized treatment will be administered by slow IV infusion at the induction of anesthesia.

The randomization will not be stratified.

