### 7.2 Covariates

No stratification factors will be considered in efficacy analyses as covariates.

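### SAP 10.9.1 leaves covariate adjustment of the primary DFS comparison undecided, so two primary results are possible; one must be fixed before unblinding

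*SAP*

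**What the plan says.** SAP 10.9.1 (Primary analysis) has one definite sentence on the test: "The effect of ketorolac will be assessed by comparing the 2 treatment groups by a log rank test". It names no strata or covariates. The next sentence has no main verb: it opens "Potential need for adjustment regarding the inclusion criteria defining the" high-risk profile and lists "high NLR AND/OR lymph nodes invasion AND/OR triple negative histopathology". The section also promises 95% confidence intervals without naming the quantity they belong to.

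Three other sections bear on the point:

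- 7.2 (Covariates) consists of one sentence: "No stratification factors will be considered in efficacy analyses as covariates".
- 4.6 (Randomization): "The randomization will not be stratified".
- 4.5 (Sample Size Determination) assumes a 33% reduction in recurrence, 5% type I error and 80% power, and concludes that "the number of patients eligible is of 200 (Log Rank test), randomized in a 1:1 ratio between ketorolac and placebo".

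Section 10.9.2 refers back to the primary analysis for the 5-year locoregional endpoint, so whatever is open in 10.9.1 is open there too. Section 4.3 plans no interim analysis, so the whole 5% rests on the final DFS comparison.

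**The concern.** A primary analysis should lead to one p-value by a route fixed in advance. Here the SAP itself raises a second route and leaves open:

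- whether the adjustment is made, and what would trigger it;
- when that is decided relative to unblinding;
- whether the model is a Cox regression or a stratified log-rank;
- whether the factors enter separately, as a composite or as a count, and whether NLR is continuous or cut;
- which result is primary if the two disagree.

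Section 7.2 does not close the gap. With unstratified randomisation there are no stratification factors, so its sentence either has no content or, if it was meant to exclude all covariates, conflicts with 10.9.1.

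Two things are at stake. The first is control of the type I error, if the analysis were picked on its outcome. The second is any power that the high-risk factors could add, which is secured only if they are in the model by plan.

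**Working it through.** **1. The plan's own figure.** Inputs from SAP 4.5: 33% reduction, 5% error, 80% power, 1:1, log-rank. Assumptions: two-sided test (sidedness is not stated) and the reduction read as hazard ratio (HR) 0.67 (the scale is not stated). (1.960 + 0.842)² = 7.85.

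- Schoenfeld: 4 × 7.85 / (ln 0.67)² = 31.4 / 0.1604 = 196 events.
- Freedman: (1.67 / 0.33)² × 7.85 = 25.61 × 7.85, just over 201, so 202 events.

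The figure of 200 is reproduced within 3%, as events. As patients it also arises if control risk is 60% and falls to 40.2%: HR = ln(0.598) / ln(0.40) = 0.561; Freedman events (1.561 / 0.439)² × 7.85 = 99.3, so 100; patients 2 × 100 / (0.60 + 0.402) = 200. Which reading was meant is a separate matter. Here the figure only fixes the test, the error rate and the effect size.

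**2. Simulation set-up.** 200 patients, 1:1, exponential DFS, common follow-up. Three binary factors with prevalences 50%, 50% and 20%, keeping only patients with at least one because the factors define inclusion. Each factor multiplies the hazard by 1.5, 2 or 3. Control event risk is 30% or 60%. All of these are assumptions; the SAP gives none of them. There were 6,000 null trials and 4,000 trials at HR 0.67 per setting.

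**3. Type I error (%), two-sided 5%**

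| Control risk | Factor HR | Log-rank | Adjusted Cox | Better of the two | Better of three* |
|---|---|---|---|---|---|
| 30% | 1.5 | 5.13 | 5.23 | 6.13 | 6.73 |
| 30% | 2 | 4.88 | 4.52 | 6.12 | 6.70 |
| 30% | 3 | 5.40 | 4.95 | 7.40 | 7.90 |
| 60% | 1.5 | 4.85 | 4.77 | 5.95 | 6.43 |
| 60% | 2 | 4.92 | 4.85 | 6.73 | 7.43 |
| 60% | 3 | 5.08 | 5.17 | 7.52 | 8.25 |

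*Adds a log-rank stratified by the three factors. Simulation standard error at 5%: √(0.05 × 0.95 / 6000) = 0.28 points. Each single test holds 5% within that error.

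**4. Power (%) at HR 0.67**

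| Control risk | Factor HR | Log-rank | Adjusted Cox | Change (points) |
|---|---|---|---|---|
| 30% | 1.5 | 29.62 | 29.20 | −0.42 |
| 30% | 2 | 27.68 | 28.52 | +0.84 |
| 30% | 3 | 26.28 | 29.88 | +3.60 |
| 60% | 1.5 | 51.35 | 52.98 | +1.63 |
| 60% | 2 | 48.28 | 53.92 | +5.64 |
| 60% | 3 | 42.60 | 54.75 | +12.15 |

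Standard error of each power figure: at most √(0.5 × 0.5 / 4000) = 0.8 points. The levels are below 80% because these settings yield about 51 to 108 events, against the 196–202 of step 1. They would be higher under the HR 0.561 reading, which was not simulated.

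**5. Sensitivity to set-up.** Runs with follow-up spread over 2 to 5 years, other prevalences (50%, 20%, 40%, at least one factor required) and 25% or 40% two-year control risk gave 6.4–7.4% for the better of two tests and a power change of 1 to 11 points. A further set gave about 6–7% in most settings and 0 to 9 points; one setting reached 8.6%, but its single tests also ran high, at about 6%.

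**6. Would the question of adjustment arise?** Requiring at least one factor removes 0.5 × 0.5 × 0.8 = 20% of draws, so the prevalences in step 2 become 62.5%, 62.5% and 25%. With 100 per arm, the chance of a difference of 10 points or more is about 14% for each of the first two (standard error √(2 × 0.625 × 0.375 / 100) = 6.8 points) and about 10% for the third (6.1 points). Treating them as independent, the chance for at least one is 1 − 0.856 × 0.856 × 0.897 = 34%. That is a realistic prospect, not a near-certainty.

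**The case against.** The strongest reply is that the SAP has only one affirmative primary test. The log-rank is what 10.9.1 says will be done, what 4.5 sizes the trial on, and what 7.2 is compatible with. The adjustment sentence looks like a leftover drafting note, like the unanswered query that opens section 10 and the appendices still to be supplied. Nothing says that the decision would follow unblinding, and the inflation arises only if the smaller p-value is taken. All of that stands, and it limits the point to an ambiguity. It does not remove it: the sentence is in the primary analysis section, and no other section withdraws it.

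Three stronger readings are tempting, and the document does not support them.

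- A reader might infer that the p-value will be chosen after seeing results. The SAP does not say so; it merely fails to exclude it.
- A reader might infer that chance imbalance makes the unadjusted log-rank invalid. It does not: that test held 4.9–5.4% in every setting above.
- A reader might infer that omitting the factors biases the treatment effect towards no effect. An unadjusted and an adjusted hazard ratio are different quantities (marginal and conditional), so a gap between them is not bias. The SAP names no hazard ratio in any case.

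**Conclusion.** The point holds as a defect in prespecification. Section 10.9.1 permits two primary results for DFS, and neither 7.2 nor any other section says which decides.

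If the choice were made on the results, the two-sided 5% error would rise to roughly 6–7.5% with two candidate tests. It would reach 6.4–8.3% if a stratified log-rank were also tried. The rise is modest because the tests are highly correlated.

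The power argument is secondary and conditional. At HR 0.67 a prespecified adjustment changes power by about 0 to +12 points: negligible with weak factors or few events, material with strong factors and many events. Larger benefits should not be claimed, since the SAP supports no effect beyond the 33% reduction and gives no prognostic strengths.

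All sizes rest on the assumed prevalences, factor hazard ratios of 1.5–3, binary coding of all three factors (including NLR) and control risks of 30% and 60%. The ambiguity itself rests on the text alone.

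**What to change.** Before unblinding, replace the open sentence in 10.9.1 with one primary analysis:

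- a Cox model for DFS on the FAS with treatment, nodal invasion, triple-negative status and NLR as fixed covariates, whatever the observed balance;
- covariate values as recorded for eligibility before randomisation (Table A also schedules histology at discharge and follow-up, which should not be used here);
- coding written out, including whether NLR is continuous or cut, and where;
- the hazard ratio with its 95% CI as the reported effect;
- the unadjusted log-rank on the FAS labelled as a sensitivity analysis.

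Reword 7.2 to match. Name the Cox model only: offering a stratified log-rank as an alternative would leave two candidate tests again, and it cannot take NLR as a continuous covariate.

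If the sponsor prefers to keep the log-rank on which the sample size was based, delete the open sentence and label the adjusted Cox model as the prespecified sensitivity analysis. That removes the multiplicity equally well but forgoes the possible power gain.

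The cost is SAP wording. The covariates are inclusion criteria, so they should already be on record. The downside of the adjusted primary is small: it relies on the Cox model, and it estimates a conditional rather than a marginal hazard ratio.

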#### 10.9.2 Secondary analyses

The 5 years locoregional RR will be analyzed in a similar way as the primary analysis.

Locoregional RFS, DFS, MFS and OS will be summarized using Kaplan-Meier plots. The Kaplan-Meier estimate of the event times will be presented with 95% confidence intervals. These summaries will be done on the FAS population.

The effect of ketorolac will be assessed by comparing the 2 treatment groups by a log-rank test.

.

### 10.10 Safety Analyses

All summaries will be performed on the Safety Analysis Set population.

#### 10.10.1 Serious Adverse Events

The number of events and number and percentage of patients with SAEs will be summarized by treatment group and overall. Similar summaries will be produced for: drug-related SAEs, SAEs by maximum severity grade, SAEs leading to death. These summaries will be tabulated overall and by treatment group for the FAS. Supportive listings will be provided.

#### 10.10.2 Cardiac and gastro-intestinal events

Cardiac and gastro-intestinal events will be tabulated overall and by treatment group. Similar summaries will be produced for events leading to death. Supportive listings will be provided.

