### 4.2 Study Events Flow Chart

Table A provides a detailed description of the schedule of events.

Table A: Schedule of events

|  | **Screening** | **Treatment** | **Hospital discharge** | **Follow-up at 1, 2, 5 years** |
| --- | --- | --- | --- | --- |
|  | **D-21 to D0** | **D0** | **D8** | **1, 2, 5 years** |
| Written consent | X |  |  |  |
| Inclusion/exclusion criteria | X | X |  |  |
| Randomization |  |  |  |  |
| Baseline data | X |  |  |  |
| Medications | X |  | X | X |
| Histology |  |  | X | X |
| Hospital discharge |  |  | X |  |
| Follow-up at 1 year |  |  |  | X |
| Follow-up at 2 years |  |  |  | X |
| Follow-up at 5 years |  |  |  | X |
| Chemotherapy |  |  | X | X |
| Radiotherapy |  |  | X | X |
| Chronic pain |  |  |  | X |
| Locoregional recurrence assessment |  |  |  | X |
| Distant metastases |  |  |  | X |
| Tumor biomarkers |  |  |  | X |
| Cardiovascular assessment |  | X | X | X |
| Gastro-intestinal assessment |  | X | X |  |
| Blood loss |  | X | X |  |
| Serious Adverse Event |  | X | X |  |
| Death information | X | X | X | X |
| Unblinding |  | X |  |  |
| Screening Log | X |  |  |  |

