# SAFETY VARIABLES

The safety variables include:

- - post-operative pain (CRF pain scales, post-operative pain medications and CRF16 chronic pain)
  - peri- and post-operative blood loss. (<note to programmer: CRF perioperative blood loss and CRF60)
  - Serious adverse events (note to programmer: CRF70)

Cardiac events (CRF40) and gastro-intestinal events (CRF50).

A Serious Adverse Event (SAE) is defined as any AE that results in death, is life threatening, requires inpatient hospitalization or prolongation of existing hospitalization, results in persistent or significant disability/incapacity, or is a congenital anomaly/birth defect. Drug relationship will be assessed as above.

SAEs will be considered only during the 30 days after the administration of the study product (single administration, first=last).

In the event that a partial Start Date (month/year or year) is available, and month/year or year occurs before that of first treatment dose, the AE is considered as non-treatment emergent. However, if month/year or year occurs on or after the date of first treatment dose, the following cases will be considered:

- if month/year is available and month/year of Start Date >= month/year of first treatment dose, the AE is treatment emergent and Start Date will be estimated as the first day of the month;
- if only year is available and year of Start Date >= year of first treatment dose, the AE is treatment emergent and Start Date will be estimated as Jan. 1 of that year.
- In the event that the Start Date is completely missing, Stop Date will be used to determine when the AE resolved. If the AE stopped before first treatment dose, the AE will be considered as non-treatment emergent; otherwise, if the AE stopped on or after first treatment dose or is ongoing, the AE will be considered as treatment emergent and the Start Date of the event will be estimated as first treatment dose.

The estimated start dates will not be listed.

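### Section 10.10.2 sets no time window for cardiac events, so one percentage would pool the peri-operative period with up to 5 years of follow-up after a single dose

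*SAP*

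**What the plan says.** Exposure is one administration. Section 4.6 states that "the randomized treatment will be administered by slow IV infusion at the induction of anesthesia".

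Table A (section 4.2) follows three kinds of safety information for different lengths of time:
- Cardiovascular: "Cardiovascular assessment | | X | X | X". The last mark falls in the column headed "Follow-up at 1, 2, 5 years".
- Gastro-intestinal: "Gastro-intestinal assessment | | X | X", with nothing after discharge at D8.
- SAEs: "Serious Adverse Event | | X | X", likewise with nothing after D8.

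The Safety Variables section gives SAEs a limit: "SAEs will be considered only during the 30 days after the administration of the study product (single administration, first=last". It identifies cardiac events only by their form, CRF40, with no window and no visit.

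For the analysis, section 10.10.2 says "Cardiac and gastro-intestinal events will be tabulated overall and by treatment group", and adds similar summaries for events leading to death. Section 10.10.1 breaks SAEs down by drug relationship, maximum severity grade and fatal outcome, but not by organ system.

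**The concern.** A table of cardiac events in a single-dose peri-operative trial should let the reader see whether the arms differ around the time of dosing. If every CRF40 event from D0 to year 5 goes into one percentage per arm, an event on the day of surgery counts the same as one in year 4. By then patients may have had the systemic therapy and radiotherapy covered in sections 10.5 and 10.6, and they will have been followed for unequal times. An early imbalance is then diluted by later events in both arms, and a chance late imbalance could be read as an effect of the dose.

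The SAP already recognises a 30-day period for SAEs. Leaving cardiac events without one means that the window may end up being chosen after the results by arm are known.

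**Working it through.** **1. Can a window be read into the text?** No figure in the plan needs reproducing, so the first check compares sections.
- In section 10.10.2, overall means both arms combined. It does not refer to a period.
- Where the SAP wants results by time it says so: section 10.7 presents pain scales at timepoints after surgery, and section 10.10.5 summarises CA 15.3 by visit. Section 10.10.2 has no such words.
- The partial-date rule in Safety Variables treats any adverse event starting on or after dosing as treatment emergent. It has no upper limit, so it does not bound cardiac events.
- Section 7.1 makes counts and percentages the default for categorical data.
- Appendix I, which is to hold the table templates, has not been supplied.

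A programmer following the current text would therefore produce one crude percentage per arm over all follow-up.

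**2. How short is the peri-operative period?** 30 / (5 × 365.25) = 30 / 1826 = 1.6% of a 5-year follow-up.

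**3. How large could the dilution be?** The SAP gives no cardiac rates, so every rate here is an assumption. Let p be the 30-day risk in an arm and r a yearly background risk, equal in both arms, with complete 5-year follow-up:

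5-year risk = 1 − (1 − p)(1 − r)^5

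Example with r = 1%: 0.99^5 = 0.951. The lower-risk arm has 1 − 0.99 × 0.951 = 5.85% and the higher-risk arm 1 − 0.96 × 0.951 = 8.70%. The ratio is 8.70 / 5.85 = 1.49.

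| 30-day risks | Background per year | 5-year risks | Risk ratio | Difference (points) | Share counted only for a later event |
|---|---|---|---|---|---|
| 1% vs 4% | none | 1.00% vs 4.00% | 4.00 | 3.0 | 0% |
| 1% vs 4% | 0.5% | 3.45% vs 6.38% | 1.85 | 2.9 | 49% |
| 1% vs 4% | 1% | 5.85% vs 8.70% | 1.49 | 2.9 | 66% |
| 1% vs 4% | 2% | 10.51% vs 13.22% | 1.26 | 2.7 | 79% |
| 1% vs 4% | 3% | 14.99% vs 17.56% | 1.17 | 2.6 | 85% |
| 2% vs 8% | none | 2.00% vs 8.00% | 4.00 | 6.0 | 0% |
| 2% vs 8% | 0.5% | 4.43% vs 10.28% | 2.32 | 5.9 | 32% |
| 2% vs 8% | 1% | 6.80% vs 12.51% | 1.84 | 5.7 | 48% |
| 2% vs 8% | 2% | 11.42% vs 16.84% | 1.48 | 5.4 | 65% |
| 2% vs 8% | 3% | 15.84% vs 21.00% | 1.33 | 5.2 | 73% |

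The last column is 1 minus the sum of the two 30-day risks divided by the sum of the two 5-year risks. The difference equals the 30-day difference times (1 − r)^5, a factor of 0.975 at r = 0.5% and 0.859 at r = 3%. That is why it barely moves.

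**4. What happens to the noise?** With 200 patients randomized 1:1 (section 4.5) there are 100 per arm. The standard error of the difference is √[(p₁(1 − p₁) + p₂(1 − p₂)) / 100].
- For 1% vs 4% at 30 days: √[(0.0099 + 0.0384) / 100] = 2.2 points.
- Pooled to 5 years with a 3% background: √[(0.1274 + 0.1448) / 100] = 5.2 points, for a difference of 2.6.

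Nearly the same difference would be read against more than twice the random variation.

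**The case against.** Several objections carry weight.

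- **The safety objective is already windowed.** Section 3.2 bases the safety profile on SAEs, which have a 30-day limit. A reader might infer that the plan would hide any peri-operative cardiac signal. It would not: a serious cardiac event within 30 days enters the SAE summaries and listings. What remains exposed is non-serious early events, and the comparison of cardiac events as a group, because the SAE tables have no organ-system breakdown.
- **Pooling is inferred from silence.** The SAP leaves table details to Appendix I, which is pending, so a split could still appear there. This stands as far as it goes, but nothing in the current text asks for one.
- **Late events may be of interest.** A reader might infer that events after day 30 are unrelated to treatment. The SAP does not show that. It plans cardiovascular assessment to 5 years, and the trial's premise is that a single dose alters long-term outcomes. Late events should be kept and shown separately.
- **Differing death counts are not a contradiction.** A fatal cardiac event in year 3 would appear under section 10.10.2 but not among fatal SAEs. A reader might call this inconsistent. The two tables use different forms and the SAE window is stated, so different counts are expected. A footnote is enough.
- **The ratio is not a planned statistic.** The SAP plans only counts and percentages for cardiac events, and the absolute difference hardly changes. This is correct, and it limits the claim to dilution and noise. Readers of such a table will still compare the two percentages.

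**Conclusion.** The point holds in a limited form. Section 10.10.2 gives cardiac events, and those leading to death, no window and no visit split, although they are assessed from D0 to 5 years after one dose. Under the assumed rates, a 30-day risk ratio of 4.0 would appear as 1.17 to 2.32 over 5 years, and between 32% and 85% of the patients counted would be there only because of a later event. The direction is the same across the range; the size depends wholly on the assumed rates.

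The conclusion also assumes that CRF40 is the form behind the cardiovascular row of Table A, that background risk is equal in both arms, and that follow-up is complete. It does not reach gastro-intestinal events, whose assessment ends at D8, and it touches no efficacy analysis.

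**What to change.** In section 10.10.2, and in the matching templates of Appendix I:

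1. Tabulate cardiac events separately for day 0 to day 30 after dosing, which is the SAP's own SAE window, and for the time after day 30. The second part is descriptive, by follow-up visit or interval.
2. Apply the same split to cardiac events leading to death.
3. If CRF40 records no event dates, split by visit: D0 and D8 against the 1-, 2- and 5-year follow-ups.
4. Add a footnote that the SAE table covers 30 days only, so its death count can differ from the cardiac table.

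The cost is SAP wording and one extra split in a planned table, with no new visits. One weakness remains: after D8 the next scheduled assessment is at 1 year, so non-serious events on days 9 to 30 may be recorded only then, from recall. The split should be fixed before unblinding, so that the window is not chosen with the results in view.

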#### 10.10.3 Chronic pain

Pain scales will be tabulated overall and by treatment group. Supportive listings will be provided.

